#### Bio-aerosol sampling and molecular detection

We will collect Mtb particles from the air using mobile bio-aerosol sampling devices (Dry Filter Unit (DFU)1000, Lockheed Martin Integrated Systems, Gaithersburg, Maryland, USA). The DFU 1000 is a portable biological air sampler. Ambient air is drawn through 1 µm polyester-felt filters at a rate of ~1000 L/min via an electrical blower. The DFU is a useful collection system for low concentration aerosols, capturing particles of 1 µm or larger, and allowing easy access for the retrieval of filters. One DFU will be placed in the waiting room and the other in the TB treatment room (figure 1). Each DFU collects air for 7 hours (two periods of 3.5 hours) every day onto two filters. Due to logistical and human resource limitations, we will be able to change filters only two times per day. Therefore, we decided to run the mobile bio-aerosol sampling devices during the busiest time at the clinic, between 07:00 and 14:00. All other data will be collected from 07:00 to 16:00.

As previously described,^17^ duplicate filters from each sampling session will be transferred to 50 mL Falcon tubes and vortexed in sterile phosphate buffered saline (with 0.05% Tween 80). Following centrifugation at 3750 rpm for 15 min, filters will be removed and the pellet subjected to DNA extraction. DNA from Mtb cells will be extracted using an in-house lysis buffer with subsequent pelleting (centrifugation 13 000 rpm for 10 min) of DNA and resuspension in 50 µl of Tris-EDTA buffer (10 mM Trist, 1 mM EDTA, pH 8.0). Given that droplet digital PCR (ddPCR) is relatively robust against inhibitors, no further DNA purification will be required. The primer/probe combinations and reaction conditions for Mtb-specific ddPCR have been described.^16^ Samples with known amounts of purified Mtb DNA (0.01 ng and 0.001 ng) will be included to serve as positive and nuclease-free water as negative control. The data generated from the ddPCR reaction will be analysed via the Umbrella pipeline,^25^ using wells with a minimum of 10 000 droplets.

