### Statistical analyses

We will describe the data and examine associations between sources of data and then use results to parameterise a mathematical model (table 1). The statistical analysis will quantify the joint association between the clinical and environmental variables and the number of Mtb particles measured by the mobile aerosol sampling. To this end, we will use Poisson regression, with the number of Mtb particles by the period of time as the dependent variable, considered as a proxy measure for the risk of TB transmission. As this variable is measured by periods of 3.5 hours, the other variables will be aggregated over the same periods. We will consider all combinations of independent variables, including second-order interactions, and compare the model using standard model selection methods. We will use variable selection methods in a Bayesian framework, including the deviance information criterion and the leave-one-out information criterion.^26^

**Table 1 T1:** Description of the measurements

Data source	Parameter	Description	Unit	Measurement taken by
CO_2_ monitor	CO_2_	Observed CO_2_ concentration in the indoor air per minute and a control in the outdoor air. Based on CO_2_ levels and people density, we will calculate rebreathed air volume, which is used as a proxy for airborne TB transmission.^16^	ppm	Minute and date
	Relative humidity	Data on the effects of relative humidity on the survival of airborne bacteria are inconsistent.^28 37^ However, a recent study found that relative humidity above 65% is associated with Mtb survival in the air.^14^	%	Minute and date
	Temperature	Temperatures above 24°C are required to reduce airborne bacteria survival.^28 37^	°C	Minute and date
Cough recording	Frequency	One of the typical symptoms of TB is coughing; coughing is also the main way of transmission.	n	Minute or day and date
	Duration	Duration of each cough is different from healthy and people with TB or other lung diseases^30^	s	Cough by minute and date
	Intensity	Intensity of each cough is different from healthy and people with TB or other lung diseases.^30^	dB	Cough by minute and date
Mobile aerosol sampling	Mtb DNA copies	Detection of Mtb particles in the air by filter or per day (07:00 to 14:00).^17^	Copies per microliters	Filter (ca.3.5 hours sampling) or per day

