*Patient data*: Numbers and characteristics of patients consulting the clinic overall will be summarised using descriptive statistics.*Video sensor data:* Raw data about individuals’ movements will be transformed into waiting times until medical consultation, number of individuals in the different locations, highly frequented areas in the clinic and the average distance between patients (ie, clustering). We will link each tracked individual to the clinical data collected from the clinic’s database (ie, TB/HIV diagnosis), using the order of arrival and time of registration.*CO_2_ data*: Measurements of CO_2_ concentration at the different locations in the clinic (waiting room, registration desk, TB treatment room), together with estimates in outdoor air, will be used to estimate the proportion of air in the different locations that was expired by individuals, the rebreathed fraction.^12^ We will use a modified Wells-Riley model appropriate for non-steady states conditions of ventilation and number of individuals to describe and calculate the shared rebreathed air in the different locations in either litre/minute or litre/day and the air exchange (litre/hour per person). Table 2 describes the parameters to calculate the shared rebreathed air and the air exchange.^13 16 27 28^The proportion of rebreathed air (*f*) will be calculated from the excess CO_2_ measured indoors, divided by the exhaled CO_2_ (*Ca*):(1)$$f=\frac{\left(C-Co\right)}{Ca}$$(see table 2 for definitions of parameters in this and the following equations).Before we can calculate the rebreathed air volume (RAV) we will need the rebreathed proportion from other people (ƒo). Therefore, we need to know the number of people (*n*) present at each time point at the clinic:(2)$$fo=f\times \frac{\left(n-1\right)}{n}$$Finally, we can calculate the RAV for each minute by multiplying ƒo and the minute respiratory volume (8 L/min, *(p*)) as:(3)Rebreathedairvolume(RAV)=(pfo)In the next step, we aim to calculate the ventilation rate (air exchange). The indoor CO_2_ generated rate is the product of the average volume of gas exhaled per person (0.13 L/s per person, *(V*)) and the CO_2_ concentration of the exhaled air:(4)$$\begin{array}{c} IndoorCO_{2}generationrateinl/s\\ perperson\left(G\right)=VxCa \end{array}$$The ventilation rate is expressed as:(5)$$\begin{array}{c} Ventilationrateinl/sperperson\\ \left(Q\right)=\frac{G}{C-Co} \end{array}$$To calculate the air exchange per hour (Equation 6) we need to know the volume of air in a given location.*Relative humidity and temperature:* We will describe changes in relative humidity and temperature over the day.*Cough sounds*: Frequency, intensity, duration of recorded coughs per time period.^29 30^*Detection of Mtb in bio-aerosol sampling*: The number of Mtb genome copies present in each sample.

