### Pilot study

We conducted a pilot study in Cape Town (South Africa) to examine the feasibility of our approach (figure 1). The pilot study took place at a primary care clinic, which incorporates HIV counselling and testing, and a TB clinic for the diagnosis and management of TB. The clinic is situated in Masiphumelele, a large settlement of formal and semiformal housing in Cape Town, which has previously been described.^35 36^ The clinic is open on workdays from Monday till Friday from 07:00 till 16:00. We studied clinic activities for over 4 weeks on workdays between July 25 and August 23 2019.

Data collection was successful overall, however, we experienced several power cuts during the pilot study. An important lesson learnt is that power banks for laptops and WiFi routers are needed, as well as Uninterruptible Power Supply (UPS) and access to a generator as back-up for the DFU and CO_2_ monitors.

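### The aerosol outcome is a concentration in Table 1 but a count in the analysis text, and the Poisson model fixed for it gives different precision for each unit

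*Protocol article*

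**What the plan says.** Under Statistical analyses the model is stated as: "we will use Poisson regression, with the number of Mtb particles by the period of time as the dependent variable". Table 1 in the same section gives the unit of the mobile aerosol measurement as "Copies per microliters", recorded per filter (about 3.5 hours) or per day. The list that operationalises the variables gives: "The number of Mtb genome copies present in each sample". The Mathematical modelling section again uses a count of genomes, now per 6-hour period, and models it as a Poisson process with time-dependent intensity.

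The laboratory steps are under Bio-aerosol sampling and molecular detection. Extraction ends with "resuspension in 50 µl of Tris-EDTA buffer", and the droplet PCR data are analysed "using wells with a minimum of 10 000 droplets". The volume of eluate put into the reaction is not given. Air is drawn "at a rate of ~1000 L/min via an electrical blower", and "Each DFU collects air for 7 hours (two periods of 3.5 hours) every day onto two filters". The Pilot study section reports that "we experienced several power cuts during the pilot study" and names an uninterruptible supply and generator as back-up for the sampler. Strengths and limitations repeats that plan. Neither model names an exposure term.

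**The concern.** A concentration and a count are different variables, and a Poisson likelihood treats them differently. It takes the variance to equal the mean on whatever scale is supplied. Dividing the data by a constant therefore makes the model believe it has less information, and multiplying makes it believe it has more. The slope does not reveal this, because it stays the same.

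The number actually counted in droplet PCR is positive droplets among accepted droplets. Copies per microlitre is derived from that number and need not be an integer. Copies per sample is that number scaled up whenever only part of the eluate is assayed. Neither printed unit is therefore sure to carry the right amount of information.

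This variable is the dependent variable in both models. The plan compares all combinations of covariates, with second-order interactions, by DIC and leave-one-out. The unit therefore affects the width of the credible intervals and can affect which factors are reported as key drivers.

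**Working it through.** The article states no sample size, power or precision for this analysis, so there is no figure of its own to reproduce. The checks below follow from its stated inputs. Assumptions are marked.

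1. **Effect of the unit on the standard error.** In a log-link Poisson model with mean μ, the information on a slope is Σμx². Scaling the outcome by k scales μ by k, so the standard error is multiplied by 1/√k. From copies per 50 µl sample to copies per µl, k = 1/50 and the factor is √50 = 7.07. Fitting the same simulated data both ways (assumed: 40 sessions) gave identical slopes and these standard errors:
   - mean count 10: 0.0545 and 0.3853
   - mean count 50: 0.0247 and 0.1749
   - mean count 250: 0.0110 and 0.0777

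   The ratio is 7.07 each time. With a null covariate and mean count 50, where copies per sample are the true counts, a 5% test rejected in 5.7% of 2,000 runs on copies per sample and in 0.0% on copies per µl.

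2. **Copies per sample when only part is assayed.** Let s be the microlitres assayed (assumed: 2 to 10). At low droplet occupancy the raw count is roughly the copies in s.
   - Copies per sample multiplies the raw count by 50/s, which is 25 to 5. The Poisson standard error is then too small by √25 = 5.0 to √5 = 2.2.
   - Copies per µl divides the raw count by s. The standard error is then too large by √2 = 1.4 to √10 = 3.2.
   - The two errors multiply back to step 1: 5.0 × 1.41 = 7.07 and 2.24 × 3.16 = 7.08 (7.07 before rounding).

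3. **Model comparison.** Scaling by k multiplies Poisson deviance differences by k, while the DIC penalty stays near one effective parameter per term. With vague priors a null term is kept when k × χ²(1) > 2. The probability is 15.7% at k = 1, 52.7% at k = 5, 77.7% at k = 25 and essentially 0% at k = 1/50. Leave-one-out differences also grow or shrink with k. Their sign should be less affected, because the held-out fit scales along with the rest, so no retention rate is claimed for that criterion.

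4. **Period and air volume.** Volume is 1000 L/min × minutes:
   - 3.5 h: 210,000 L
   - 6 h: 360,000 L, or 1.71 times as much
   - 7 h, the sampling day: 420,000 L, or 2 times as much

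   Six hours matches neither one filter period nor the two together.

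5. **Interrupted sessions.** If h hours of 3.5 are lost, the expected count becomes (3.5 − h)/3.5 of its full value. For assumed losses of 0.5, 1 and 1.75 h this is 86%, 71% and 50%, a fall of 14%, 29% and 50%. A simulation tested a null covariate at 5% (assumed: 40 sessions, mean count 50, cuts of 0.25 to 2 h, 1,000 runs per setting):
   - no cuts: 4.5% to 5.3%, with or without an offset for hours run
   - no offset, cuts unrelated to the covariate: 12.6% with 10% of sessions cut and 19.8% with 25%
   - no offset, covariate shifted by 1 SD in cut sessions: 31% and 63%
   - with the offset, cuts present: 4.0% to 5.4%

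**The case against.** The strongest reply is that every sentence describing an analysis names a count. Microlitres appear only in a table of measurements, where they can be read as the assay's output, convertible through the 50 µl resuspension. That stands. A reader might infer that the concentration is what will be modelled, but the documents do not say so. Table 1 also does not say that the microlitre is one of eluate, so the 7.07 is conditional. What the reply does not cure is step 2: the count in the variable list may itself be a scaled-up estimate.

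It is also fair that sampling is equal by design, and with equal sessions an offset is absorbed by the intercept. A reader might infer that sampled air varies by plan, or that power cuts will pass as clean air. The article supports neither. It plans back-up power for the sampler, calls pilot data collection successful overall, gives no number or length of cuts, and does not say that interrupted sessions would be analysed as full ones. A short cut lowers the count in proportion; only near-total loss would resemble clean air.

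A missing offset alone is silence in a condensed article and could be settled in a document not shown. The droplet minimum is a quality threshold: variation above it changes precision, not the level of the estimated concentration. These replies narrow the point, but the conflicting units and periods are printed in the article.

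**Conclusion.** The point holds in limited form. The outcome's unit and period are not reconciled, and the stated Poisson likelihood makes precision depend on the unit chosen. The factor between the two printed units is 7.07 on the standard error, if the microlitre in Table 1 is one of eluate. Against the raw count, copies per sample understates the standard error by 5.0- to 2.2-fold if 2 to 10 µl is assayed. There is no understatement from this source if the whole eluate is assayed. Exposure is a secondary matter that depends on interruptions or flow drift. The 14% to 50% fall in expected count and the simulated error rates rest on assumed inputs, not on pilot figures.

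**What to change.** - **Outcome and period.** Name one outcome, correct the unit in Table 1 or state its conversion, and use one period in place of 3.5 h, per day and 6 h.
- **Likelihood.** Model positive droplets as binomial out of accepted droplets, with probability 1 − exp(−m), where m is the mean copies per droplet. Take log m as the linear predictor plus log(eluate volume per droplet ÷ 50 µl × air volume). The eluate volume per droplet carries the assayed share. Covariate effects then act on copies per m³ of air.
- **Simpler alternative.** At low droplet occupancy, use the raw positive count as Poisson and add log(accepted droplets) to that offset. This is an approximation to the binomial form.
- **Exposure.** Log sampler run time, compute air volume as run minutes × flow, and aggregate covariates only over the minutes when the sampler ran.

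The cost is analysis wording, keeping droplet counts and assayed volumes, and a run-time log for each sampler. The article does not say that the sampler records run time, so the log may be an added field task.

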
**Table 2 T2:** Description of the variables to calculate the shared rebreathed air volume and air exchange as well as the parameters to construct the mathematical transmission model

Parameter	Description	Value
C	Observed CO_2_ concentration in the indoor air per minute	Observed
Co	CO_2_ concentration in the outdoor air per minute	400–420 ppm^23^
Ca	CO_2_ concentration in the exhaled air	38 000–40 000 ppm^13 38^
f	Proportion of rebreathed air	Equation
n	Number of people recorded at the location	Observed
fo	Rebreathed proportion from other people	Equation
p	Minute respiratory volume	8 L/min^38^
RAV	Rebreathed air volume	Equation
V	Average volume of gas exhaled per person	0.13 L/s per person^16^
G	Indoor CO_2_ generation rate (L/s per person)	Equation
Q	Ventilation rate (L/s per person)	Equation
vol	Volume of the room	Calculated

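### Equation 5 is the steady-state ventilation formula, although the plan says the air exchange will be calculated with a model suited to non-steady conditions

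*Protocol article*

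**What the plan says.** In the protocol article, Statistical analyses, the CO2 item opens with the method: "We will use a modified Wells-Riley model appropriate for non-steady states conditions of ventilation and number of individuals". The same sentence lists what the model will deliver: shared rebreathed air "in either litre/minute or litre/day and the air exchange (litre/hour per person"). The non-steady claim therefore covers both quantities.

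Equations 1 to 3 then give the rebreathed fraction f, the part of it that comes from other people, and the rebreathed air volume. Equation 4 sets G = V × Ca. Equation 5 follows the words "The ventilation rate is expressed as" and gives Q = G/(C − Co) in L/s per person. Table 2 defines C as "Observed CO_2_ concentration in the indoor air per minute". No restriction to equilibrium or peak CO2 is attached to Equation 5. Room volume appears only afterwards, for conversion to air changes per hour; that step is called Equation 6, but the equation is not printed.

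Ventilation matters in two other places. Hypothesis 3 in the Introduction links low ventilation to higher transmission risk, and Mathematical modelling names increased ventilation as a scenario to be evaluated.

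**The concern.** CO2 in a room lags behind the number of people in it. In a clinic that opens at 07:00 and whose occupancy changes through the day, the CO2 excess is too low for the current head count while the room fills and too high while it empties. A formula that assumes equilibrium reads the first as good ventilation and the second as poor ventilation. The lag is longest where air exchange is lowest, so the error is largest in the rooms of most interest under hypothesis 3.

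Equation 5 is the only ventilation estimate printed. A scenario of increased ventilation needs a baseline, and this is the only one the article defines.

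**Working it through.** **Inputs from Table 2.** Ca is "38 000–40 000 ppm"; Co is 400–420 ppm; V ("Average volume of gas exhaled per person") is 0.13 L/s; C and n are observed; room volume is to be calculated, with no value given. The article states no ventilation result to reproduce.

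**Equations 4 and 5 as printed.** G = 0.13 × 0.038 to 0.13 × 0.040 = 0.00494 to 0.0052 L/s per person. At C = 1000 ppm, Q runs from 0.00494/0.000600 = 8.2 to 0.0052/0.000580 = 9.0 L/s per person.

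**Where Equation 5 comes from.** For a well-mixed room,

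vol × dC/dt = n × G − Qroom × (C − Co).

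Setting dC/dt = 0 gives Qroom/n = G/(C − Co), which is exactly Equation 5. The storage term vol × dC/dt is missing.

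**Relation to f.** Equation 1 is f = (C − Co)/Ca. Hence Q = V × Ca/(C − Co) = V/f. With V and Ca held constant, Q is a fixed multiple of the reciprocal of f.

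**Size after a step change.** The air-exchange rates (ACH, per hour) below are assumptions. With t in hours, the ratio of estimated to true ventilation after an empty room fills at once is 1/(1 − exp(−ACH × t)). It does not depend on room volume, head count or G.

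| ACH | 10 min | 30 min | 60 min | Time to within 10% |
|---|---|---|---|---|
| 1 | 6.5 | 2.5 | 1.6 | 144 min |
| 2 | 3.5 | 1.6 | 1.2 | 72 min |
| 3 | 2.5 | 1.3 | 1.05 | 48 min |
| 6 | 1.6 | 1.05 | 1.00 | 24 min |
| 12 | 1.16 | 1.00 | 1.00 | 12 min |

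If occupancy halves from equilibrium, the ratio for total ventilation (n × Q) is 1/(1 + exp(−ACH × t)). At 10, 30 and 60 minutes this is 0.54, 0.62 and 0.73 at 1 ACH; 0.62, 0.82 and 0.95 at 3 ACH; and 0.88, 1.00 and 1.00 at 12 ACH.

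**Size over an assumed day.** Assumptions: 200 m³, Ca 39 000 ppm, Co 400 ppm; occupancy rises from 0 to 40 over 2 h, stays flat for 2 h, then falls to 5 over 5 h.

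- Minutes with n × Q more than 20% off: 63%, 38%, 29%, 11% and 5% at 1, 2, 3, 6 and 12 ACH.
- First 3.5-hour session, from mean n and mean CO2 excess: ratio 1.56, 1.25, 1.15, 1.07 and 1.03. Second session: 0.91, 0.93, 0.95, 0.97 and 0.98.
- First session, averaging minute-level n × Q and dropping minutes with CO2 excess below 50 ppm: 2.3 at 1 ACH, 1.3 at 3 and 1.05 at 12.

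On the first-session figures from mean n and mean excess, a true 12-to-1 contrast between rooms at 12 and 1 ACH would read as 12 × 1.03/1.56 = 7.9 to 1.

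**Check of the remedy.** Qroom = (n × G − vol × dC/dt)/(C − Co) returned a ratio of 1.00 at 30, 60 and 300 minutes for all five rates. The simulated data are noise-free and follow the same balance, so this confirms the algebra but not performance in a real clinic.

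**The case against.** The best defence is that little of the planned inference rests on Q. The first transmission model uses occupancy, rebreathed fraction and coughs. The listed extensions are patient characteristics, shared rebreathed air, patient flow and other cough measures. Equations 1 to 3 use the concurrent CO2 excess and do not need equilibrium. This stands. A reader might infer that the association between ventilation and airborne Mtb will be biased; the article does not support that, because no named model includes Q. It could enter only through the general intention to consider all combinations of independent variables, or because Table 2, whose title also covers the parameters of the transmission model, lists it.

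A reader might also infer that ventilation is badly misestimated whenever occupancy changes. That is too broad. At 6 to 12 air changes per hour the error after a step change is brief, and 3.5-hour averages of n and CO2 excess are within about 15% at 3 or more. Over the whole 07:00 to 14:00 window of the assumed day, the same kind of average gives 1.14 at 1 ACH and 1.04 at 3, because filling and emptying partly offset. Against this, the morning session at 1 ACH is still 1.56, averaging minute-level values does worse, and the article does not say which average will be used.

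Finally, the article is condensed and Equation 6 is not shown. That limits what can be said about the final summary, but Equation 5 is printed in full and contradicts the sentence that introduces the method.

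**Conclusion.** The point holds as an inconsistency between the stated method and the printed formula. The article promises a non-steady method for the air exchange and supplies the steady-state solution, applied to minute-level CO2 without restriction. The direction of the error (too high while filling, too low while emptying) and the identity Q = V/f need only the well-mixed balance and the article's own equations.

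The size cannot be fixed from the article. It is material at about 1 to 2 air changes per hour and small at 6 to 12 once a step change is half an hour old; a slow, continuing fill prolongs it. These figures rest on assumed air-exchange rates, a well-mixed single zone and, for the daily figures, an assumed room and occupancy pattern.

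The ventilation estimates, comparisons of ventilation between clinics under hypothesis 3 and the baseline for the increased-ventilation scenario are affected. The rebreathed-air quantities and the first transmission model are not.

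**What to change.** Either of two changes removes the contradiction.

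1. Estimate room ventilation from vol × dC/dt = n × G − Qroom × (C − Co), fitted to the minute-level C, n and Co and the calculated room volume. Fit over windows short enough for ventilation to be roughly constant, since holding it fixed over a whole 3.5-hour session would sit badly with natural ventilation. State the well-mixed assumption, and report Qroom, Qroom/n and air changes per hour in consistent units.
2. Keep Equation 5, apply it only to periods near equilibrium by a stated criterion, and limit the non-steady wording to the rebreathed-air calculation.

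If Q from Equation 5 is kept, do not interpret it as a driver separate from f.

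The cost is a little more analysis work. No new measurement is needed. Option 1 relies on treating each room as a single well-mixed zone; option 2 discards the periods of changing occupancy.
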